### Primary outcome

#### Body composition

Body mass and height will be measured using a digital scale (Yaohua Weighing System Co., Shanghai, China) and a wall-mounted stadiometer (TANITA, Tokyo, Japan), respectively. Body composition and fat distribution will be measured using dual energy X-ray absorptiometry (DXA) (GE Lunar Prodigy, Madison, Wisconsin, United States)). The software (ENCORE, version 10.50.086, GE, Madison, Wisconsin, United States)) will be used to analyze total lean mass (TLM), total fat mass (TFM), total body fat percentage (%TBF), android fat percentage (%AF), and gynoid fat percentage (%GF).

### Secondary outcomes

#### Cardiorespiratory fitness

Peak oxygen consumption (VO_2peak_) for all participants will be measured using the Cosmed (K4b2) portable metabolic system. Expired respiratory gases will be collected on a breath-by-breath basis during a submaximal treadmill (H/P/Cosmos Pulsar 4.0, Cosmos Sports & Medical Ltd., Nussdorf- Traunstein, Germany) test. Exercise will start at a speed of 2 km/h, which will be increased every 2.5 minutes by 1 km/h until 8 km/h is reached. The criterion of exercise termination will be 80% of the maximum heart rate (HR_max_). Trained research assistants will record heart rate and power output data at the end of each stage. Heart rate will be measured using a polar heart rate monitor (Polar Electro, Kempele, Finland).

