### Sample size estimation

Sample size estimation in this RCT is based on the expected fat loss following four weeks of hypoxia exposure plus exercise and dieting. The data of our preliminary experiment showed that the means of fat percentage decrease in the normoxia and hypoxia groups were 3.1 and 6.0% respectively, and the standard deviation of the change was about 3%. It is estimated that a sample size of 17 participants per group will be required to observe a similar result with a power of 80%. Considering a 15% dropout and exit rate, we will recruit 40 subjects with 20 in each group.

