Instead of using continuous hypoxic exposure such as high altitude, we choose to use intermittent hypoxic exposure, which has been recommended as an option for the free-living obese population [30]. The effect of intermittent hypoxia exposure on weight reduction has been reported previously. In a model of diet-induced obese mice, it has been shown that intermittent hypoxic exposure induced decreases in body mass, blood glucose levels, and cholesterol erythropoietin concentrations [27,31]. In a few human studies, the synergistic effect of exercise and hypoxia in treating obesity and associated metabolic disorders has been demonstrated, where low intensity exercise training at normobaric hypoxic condition (15% O_2_) led to more weight loss and greater improvement in metabolic health compared to training at ambient conditions (21% O_2_) [32-34]. However, further evidence-based studies are needed to carefully evaluate the therapeutic value of hypoxia and the model of utilization in treating obesity, especially in children. Intermittent hypoxia exposure, as used in the ‘sleep high and train low’ paradigm has been proposed for endurance athletes to maximally enhance their endurance exercise capabilities, however the clinical use of intermittent hypoxia in the management of cardiometabolic diseases has rarely been tested. Our study will be the first to evaluate the effect of ‘sleep high and train low’ on weight loss in obese adolescents. Through monitoring a wide spectrum of health indices including blood pressure, heart rate, vital capacity, blood glucose and insulin levels, blood lipid profile, and immune function we will careful monitor any possible side effects associated with hypoxia exposure.

Furthermore, we will investigate the mechanism for the effect of hypoxia on weight management. We will focus on the regulatory effect of ‘sleep high and train low’ on gastrointestinal hormones levels. In addition, we hypothesize that the cytokine IL-6 might also play a role in mediating the appetite regulatory effect of exercise (positive effect) and hypoxia (negative effect). The clarification of mechanisms leading to weight loss in ‘sleep high and train low’ might provide information for the development of new strategies in combating obesity in the future.

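### VO2peak is described as measured, but the test is submaximal and ends at 80% of maximum heart rate, so any peak value would be an estimate

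*Protocol article*

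**What the plan says.** All the relevant text is in one paragraph of the protocol article, Secondary outcomes, Cardiorespiratory fitness.

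- The outcome and how it is obtained: "Peak oxygen consumption (VO_2peak_) for all participants will be measured using the Cosmed (K4b2) portable metabolic system".
- The type of test: "Expired respiratory gases will be collected on a breath-by-breath basis during a submaximal treadmill" test.
- The ramp: the speed starts at 2 km/h and is "increased every 2.5 minutes by 1 km/h until 8 km/h is reached".
- The end of the test: "The criterion of exercise termination will be 80% of the maximum heart rate".
- The stage data: "Trained research assistants will record heart rate and power output data at the end of each stage".

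The paragraph mentions no step from submaximal data to a peak value. It also does not say what happens to a child who is at 8 km/h but still below 80% of maximum heart rate (HRmax).

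Elsewhere, the Discussion lists heart rate among the indices to be followed for possible side effects of hypoxia: "Through monitoring a wide spectrum of health indices including blood pressure, heart rate, vital capacity". VO2peak is not named in the list of secondary outcomes under Outcome assessments, in the three hypotheses in the Background, or in the sample size section.

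**The concern.** The outcome named and the procedure described do not match. A peak oxygen uptake is the highest value a child can reach. A test that is submaximal by design and stops at a fixed fraction of HRmax ends before that point, so its highest reading is set by the stopping rule.

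Two consequences follow. First, if the trial reports a measured VO2peak by arm, it reports a quantity that this test did not observe. Second, because heart rate triggers the stop, the recorded uptake reflects how heart rate responds to work as well as aerobic capacity. Anything that moves the heart-rate response, including the intervention, could move the recorded value.

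**Working it through.** **The plan's own figure.** No sample size, expected value or standard deviation is given for VO2peak. The only power statement concerns body fat (decreases of 3.1 and 6.0, standard deviation about 3, 80% power). Taking the 0.05 level as two-sided, the normal approximation gives n = 2 × (1.96 + 0.8416)² × 3² / 2.9² = 16.8, so 17 per group. Allowing for 15% dropout, 17 / 0.85 = 20 per group. Both figures match the plan, and neither involves VO2peak.

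**The definitional check.** This carries the point and needs no assumption.

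1. The outcome is a peak, said to be measured.
2. The test is called submaximal and has one stated termination criterion, 80% of HRmax.
3. A child who follows the procedure stops on reaching that heart rate. The highest uptake seen is therefore the uptake at that heart rate, not at maximal effort.
4. Going from that value to a peak requires a prediction step. With such a step the outcome is estimated; without it the outcome is not a peak. On neither route is a peak measured.

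The ramp from 2 to 8 km/h has 7 speeds, and 8 km/h is reached after 6 × 2.5 = 15 minutes. The text does not say whether a child below the heart-rate criterion then continues at 8 km/h or stops.

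**Illustration of size.** These inputs are assumptions, not document figures: oxygen uptake linear in heart rate, with the fraction of peak equal to the fraction of heart-rate reserve; HRmax 195 to 205; resting heart rate (HRrest) 65 to 85 beats per minute.

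- Uptake at the stop as a fraction of peak: (0.8 × HRmax − HRrest) / (HRmax − HRrest).
- Relative rise in that value if heart rate is 5 beats lower at every submaximal uptake and true peak is unchanged: 5 / (0.8 × HRmax − HRrest).
- Relative rise in a peak estimated by extending the same shifted line to the unchanged HRmax: 5 / (HRmax − HRrest).

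| HRmax | HRrest | Uptake at stop / peak | Rise at stop | Rise in extrapolated peak |
|---|---|---|---|---|
| 195 | 65 | 91/130 = 70.0% | 5/91 = 5.5% | 5/130 = 3.8% |
| 195 | 85 | 71/110 = 64.5% | 5/71 = 7.0% | 5/110 = 4.5% |
| 205 | 65 | 99/140 = 70.7% | 5/99 = 5.1% | 5/140 = 3.6% |
| 205 | 85 | 79/120 = 65.8% | 5/79 = 6.3% | 5/120 = 4.2% |

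The 5-beat shift only sets the scale. The effect is proportional, so each beat moves the value at the stop by about 1/99 = 1.0% to 1/71 = 1.4%. The documents give no shift of any size or direction.

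**The case against.** The strongest reply is that this is condensation. Heart rate is recorded at every stage and gas is collected breath by breath, which are the data needed to estimate a peak from a submaximal test. The equation and the source of HRmax may well be in the full protocol, and nothing says the highest observed uptake will be reported as VO2peak. This stands in part: a missing equation is no fault in an article. But the printed words still conflict, because an estimate made with an undescribed equation is not a measurement.

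A reader might go further and infer that the arm comparison is biased and that no fitness conclusion could be sound. The documents do not support that. Heart rate appears in the Discussion as one item in a general safety list, and nothing is said about the heart-rate response to a workload after nightly hypoxia. Both arms train alike, so a training effect on submaximal heart rate bears more on change over time than on the group contrast. Reaching more work at a given heart rate is also part of what a submaximal test is meant to detect.

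A reader might also take 8 km/h as a second stopping rule that caps fitter children at a common workload. The text gives only the heart-rate criterion, and continuing at 8 km/h until it is met is equally consistent. What stands is that the case is not addressed.

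Finally, it is fair to say that renaming the outcome would not remove a heart-rate-driven shift if one existed, and that fitness plays a minor part in this trial.

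**Conclusion.** The point holds as an error of definition: a measured VO2peak cannot come from the test described. This rests on the text of one section alone. The gap between the recorded value and a true peak is about 29% to 35% of peak under the stated assumptions (100% minus 71% and 65%); other heart-rate values would change it. A difference between arms caused by hypoxia acting on heart rate is possible but not shown, and the 5% to 7% figure for a 5-beat shift shows sensitivity, not an expected bias. What is at stake is the wording of any fitness conclusion. The primary outcome, the sample size and the three stated hypotheses do not depend on it.

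**What to change.** Reconcile the outcome name with the test description in the Cardiorespiratory fitness section, leaving the exercise test unchanged. One of two wordings would do.

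1. **Name what is recorded.** Define the outcome as VO2 at 80% of HRmax, with VO2 and heart rate at a common treadmill stage that all children reach, and make no VO2peak claim. The label is then accurate, although the value at the stop and the heart rate at a common stage still reflect the heart-rate response, and the report should say so.
2. **Define an estimate.** Call the outcome estimated VO2peak, obtained by extending each child's stage-wise line of VO2 on heart rate to HRmax. State how HRmax is obtained, and state the assumption that the intervention does not alter the relation between heart rate and VO2.

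Under either wording, state how a child who reaches 8 km/h below 80% of HRmax is handled in the outcome definition.

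The cost is a change of label and one analysis definition. Stage-end heart rate and breath-by-breath gas data are already to be collected, so no new measurement is needed.

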#### Blood analyses

Fasting blood samples (2 mL, 12-hour fasting) will be obtained at baseline, post-intervention, and at two months follow-up. Serum levels of gastrointestinal hormones including leptin, ghrelin, PYY, CCK and GLP-1, as well as cytokine IL-6, will be measured using commercially available ELISA kits (R&D Systems, Minneapolis, Minnesota, United States). As reported, the lower limit of sensitivity of the assays will range between 0.8 pg/mL and 10 pg/ml. The intra-assay coefficient of variation (CV) will be less than 5% and the inter-assay CV will be less than 10%. Absorbance will be read at 450 nm wavelength using a microplate reader (Bio-Rad 550, Bio-Rad, Hercules, California, United States).

#### Appetite assessment

Children’s appetite at baseline, during, and post-intervention, and during follow-up will be assessed via a simple eight-item appetite questionnaire (Additional file 1). The questionnaire was developed by modifying the eight-item Council on Nutrition Appetite Questionnaire (CNAQ). The CNAQ is a short, simple, appetite assessment tool, which has been validated and proved to be able to predict weight loss in community-dwelling adults and nursing home residents [29]. We modified the CNAQ to reflect the nature of our intervention.

### Data management and statistical analysis

Data generated in the study will be collected and summarized using mean (standard deviation) values. Group differences in demographical and clinical characteristics at baseline will be tested using a two-sample t-test for quantitative data and chi-square test for qualitative data. Repeated measures analysis of variance (RM ANOVA) will be used to analyze the main effect of treatment and potential time-by-treatment interactions. For these analyses, parametric assumptions of the normality and homoscedasticity will be checked using standard tests and graphical methods. If those assumptions are violated, data transformation and non-parametric procedures will be considered sequentially. Multivariate regression analysis will be performed to analyze the relationship between changes in body composition, appetite score, and gastrointestinal hormones following intervention and during follow-up. Multiple models will be developed and tested for different sets of outcome measures and regressor variables. All statistical analyses will be performed using the Statistical Package for the Social Sciences (SPSS, Inc., Chicago, Illinois, United States) for Windows version 18.0, and a significance level of 0.05 will be used.

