**Methods/Design:**

In this randomized parallel group controlled clinical trial, 40 obese adolescents (20 boys and 20 girls, 11 to 15-years-old), will be recruited from a summer weight loss camp at the Shanghai University of Sport, China. Participants will be stratified by gender and randomly assigned to either the control group or the hypoxia group. During the four-week intervention period, both groups will exercise and eat a balanced diet. Additionally, the control group will sleep in normal conditions, while the hypoxia group will sleep in a normobaric hypoxia chamber (sleep high and train low). The primary outcome will be body composition and the main secondary outcomes will be the circulating levels of appetite regulatory gastrointestinal hormones. All the outcome measures will be assessed at baseline, after the four-week intervention, and at two months follow-up.

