### Randomization and blinding

After a participant is confirmed to be eligible and written informed consent has been obtained, she/he will be randomly assigned to the hypoxia or normoxia group. The randomization procedure, stratified according to gender, will be conducted by an independent statistician using a computerized randomization program. In order to minimize the potential bias, the exercise physiologist and the dietitian who manage the exercise training and the diet intervention will be blinded as to whether a subject will sleep in the hypoxia chamber or not. The hypoxia chamber will be prepared by an independent researcher. The researcher performing outcome assessments will be blinded to the subjects’ intervention allocation.

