### Diet modification

All participants will receive well-defined and balanced daily meals during the four-week intervention. Dietary recommendations will be individualized based on the individual’s basal metabolic rate and will range from 1,600 to 2,000 kcal/day. The basal metabolic rate will be calculated using the Mifflin equation [28]. The caloric intake will be calculated based on the Chinese food chart. Each day, three well-balanced meals will be provided with the following calorie allocations: breakfast 35%, lunch 40%, and dinner 25%. Each meal comprises 30% protein, 20% fat, and 50% carbohydrate by energy. Animal and vegetable oil and starch-rich food will be minimized, while the intake of vegetables, fruits, bean products, rabbit meat, beef, pork, and cellulose will be increased. This prescribed diet includes pivotal nutrients such as vitamins, minerals, essential amino acids, fiber, and polyunsaturated fatty acids.

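### Baseline is significance-tested between randomised arms and no outcome model adjusts for it; ANCOVA on the post-baseline values would be more precise and would avoid a diluted main effect

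*Protocol article*

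**What the plan says.** All statements are in the protocol article.

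- Data management and statistical analysis, on baseline: "Group differences in demographical and clinical characteristics at baseline will be tested using a two-sample t-test for quantitative data". Categorical characteristics get a chi-square test.
- Same section, on outcomes: "Repeated measures analysis of variance (RM ANOVA) will be used to analyze the main effect of treatment and potential time-by-treatment interactions". No baseline covariate is named, and gender is not named as a model term. On the error rate: "a significance level of 0.05 will be used". Sidedness is not stated.
- Randomization and blinding: "The randomization procedure, stratified according to gender, will be conducted by an independent statistician", using a computerised program.
- Abstract, Methods/Design: "All the outcome measures will be assessed at baseline, after the four-week intervention, and at two months follow-up". The Outcome assessments section gives the same three visits.
- Sample size estimation, on the expected effect from the preliminary experiment: "the means of fat percentage decrease in the normoxia and hypoxia groups were 3.1 and 6.0% respectively". For the spread, in the same percentage units, it gives: "the standard deviation of the change was about 3". From these figures the article derives 17 per group for 80% power, and 20 per group after allowing for 15% dropout.

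**The concern.** Two choices are fixed in the text.

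First, baseline is tested between arms formed by computerised randomisation. The null hypothesis of such a test is true by construction. A small p-value is a chance finding, and a large one says nothing about whether the imbalance that occurred matters for the outcome.

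Second, the baseline value of each outcome is collected on every child but is not used as a covariate. In a repeated measures ANOVA it most naturally enters as one of three levels of time. The two effects that the article names then treat it differently, and neither uses it well. The interaction subtracts it in full, whatever its correlation with the later value. The main effect averages it into the outcome, although treatment cannot have affected it.

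At stake are precision in a 40-child trial sized at about 80% power, and a clear treatment estimate at 4 weeks and 2 months.

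**Working it through.** **Inputs from the article.** Difference in mean decrease of fat percentage 6.0 - 3.1 = 2.9; SD of change 3; alpha 0.05; 80% power; 17 per group analysed, 20 per group recruited.

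**Assumptions, not in the article.** Two-sided test; equal variance at each visit; baseline-to-follow-up correlation rho between 0.5 and 0.95. For the main effect only: compound symmetry, and the 2.9-point effect held at two months.

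**1. The article's own figure.** n = 2 × [3 × (1.960 + 0.842) / 2.9]² = 16.8, rounded up to 17. Then 17 / 0.85 = 20. Both reproduce. Power at 17 per group is 80.5% by normal approximation and 78.0% by the t distribution. This calculation uses the change from baseline, unadjusted.

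**2. Baseline tests.** If ten independent characteristics were tested (the number is an assumption), the chance of at least one p < 0.05 is 1 - 0.95^10 = 40%, with randomisation working perfectly. The SD of a chance difference in means at 20 per arm is √(2/20) = 0.316 SD, so a difference above 0.3 SD arises in about 34% of trials. Such imbalance is ordinary. A p-value does not correct it.

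**3. Interaction (change from baseline) against ANCOVA.** With equal variances, the ANCOVA residual SD is 3 × √((1 + rho)/2), so the ratio of ANCOVA variance to change variance is (1 + rho)/2. Power is by normal approximation at 17 per group, for one post-baseline visit.

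| rho | Variance ratio | n per group for 80% | Power with ANCOVA | Power with change |
|---|---|---|---|---|
| 0.5 | 0.75 | 13 | 90.2% | 80.5% |
| 0.7 | 0.85 | 15 | 86.4% | 80.5% |
| 0.8 | 0.90 | 16 | 84.4% | 80.5% |
| 0.9 | 0.95 | 16 | 82.4% | 80.5% |
| 0.95 | 0.975 | 17 | 81.4% | 80.5% |

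**4. Over-correction by the change comparison.** A given baseline imbalance shifts the change contrast by (1 - rho) times that imbalance, in the opposite direction. The outcome SD implied by an SD of change of 3 is 3 / √(2(1 - rho)): 3.00, 3.87 and 6.71 at rho 0.5, 0.7 and 0.9. One SD of chance imbalance (0.316 SD) is then 0.95, 1.22 and 2.12 points. The shift is 0.5 × 0.95 = 0.47, 0.3 × 1.22 = 0.37 and 0.1 × 2.12 = 0.21 points, against a planned 2.9.

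**5. Treatment main effect with baseline as a level of time.** The expected effects at the three visits are 0, 2.9 and 2.9, with mean 2 × 2.9 / 3 = 1.93. The variance of a child's three-visit mean is SD² × (1 + 2 rho)/3. The same imbalance passes into the main effect with weight (1 + 2 rho)/3. Power is t-based.

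| rho | Power at 17 per group | Shift from a 0.316 SD imbalance |
|---|---|---|
| 0.5 | 61% | 0.63 points |
| 0.7 | 35% | 0.98 points |
| 0.9 | 14% | 1.98 points |

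The t-based power of the change contrast at one visit is 78% throughout. At rho 0.9 an ordinary chance imbalance is as large as the diluted effect of 1.93.

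The two problems run in opposite directions. A high rho makes the loss in steps 3 and 4 small and the loss in step 5 large.

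**The case against.** The strongest reply is that the plan already deals with imbalance. With baseline as a level of time, the interaction compares changes, which is unbiased over randomisations and keeps its type I error. The sample size also reproduces without adjustment. If body fat by DXA is highly correlated over four weeks, ANCOVA gains only about 2 power points. All of this stands. It limits the size of the point for the primary outcome, but it does not defend the main effect, which the article names first.

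A second reply is that a short article may leave model terms to a fuller document. That is fair for detail. Here, however, the article states both the baseline tests and the outcome model, and baseline is used only in the ways described above.

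Some stronger readings are tempting but are not supported:

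- A reader might infer that chance imbalance goes wholly uncorrected. That is true of the main effect only. The interaction removes the imbalance and goes too far.
- A reader might infer that baseline p-values will decide whether the arms are comparable, or which covariates to use. The article does not say so.
- A reader might fault the baseline t-tests for low power. Power presupposes a true population difference, which randomisation excludes.
- A reader might argue that individualised energy supply and fixed training intensity make body mass prognostic. That does not bear on fat percentage adjusted for its own baseline.

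**Conclusion.** The point holds as an inexpensive improvement to stated methods. It does not make the change comparison invalid.

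The baseline tests add nothing and should go. Relative to ANCOVA, the change comparison costs about 10 power points at rho 0.5 and about 2 at rho 0.9. The gain is therefore modest for body fat if its rho is high, and larger for the hormones and appetite score if theirs is lower. No rho is given in the article, so where each outcome falls in this range is unknown.

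The clearer fault is the main effect. If baseline is included as a level of time, a sustained effect is cut to two thirds and baseline imbalance enters the estimate. The two-thirds figure needs only that the effect be the same at both later visits. The power figures also need compound symmetry. That baseline is a level of time is inferred from the visit schedule and is not stated.

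**What to change.** 1. Replace the baseline significance tests with a descriptive table by arm.
2. For each outcome, compare the 4-week and 2-month values by ANCOVA, or an equivalent mixed model, with arm, the baseline value of that outcome, and gender (the stratification factor) as terms. Fix this before data are seen, and do not let it depend on any baseline p-value.
3. State that the treatment conclusion will not rest on a repeated measures ANOVA main effect that includes the baseline visit.

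The cost is a few sentences in the analysis section and one or two degrees of freedom per model. No new data are needed, and the planned 20 per group can stay as it is.

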It is perceivable that to promote success in longterm weight loss, hypoxia can be implemented in a traditional diet and exercise weight loss program, because the negative effect of hypoxia on appetite might be able to balance the positive effect of diet and exercise. Exercise and hypoxia have been used in combination in sports to induce maximal increase in aerobic endurance in athletes, but have rarely been used in weight loss, especially in children and adolescents. We have run several sessions of weight loss summer camps designed for obese adolescents in Shanghai, China. The effect of exercise and hypoxia on weight loss has been explored in our preliminary studies and interesting results have been generated [23,24]. As such, we are now designing a randomly controlled trial to systematically investigate the longterm weight loss effect of exercise with hypoxia in obese adolescents and determine the mediating effect of the gastrointestinal hormones. We hypothesize that: 1) exercise and hypoxia will have an additive effect on weight loss via increasing energy expenditure and suppressing appetite; 2) hypoxia use will lead to less rebound of weight loss after intervention due to its potential negating effects on compensatory changes in appetite elicited by exercise and diet in a traditional weight loss program; and 3) changes in gastrointestinal hormones (including ghrelin, PYY, CCK, and GLP-1), as well as in cytokine interleukin (IL)-6, will be associated with changes in body weight after the intervention and during follow-up.

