### Intervention

All the subjects, including both the normoxia (control) and the hypoxia groups, will undergo four weeks of aerobic exercise training and dieting (eating a balanced diet). In addition, the normoxia group will sleep in normal conditions while the hypoxia group will sleep in a normobaric hypoxic chamber every night. All the measurements will be conducted two days prior to, and post-intervention, and repeated two months later after the intervention (two months follow-up). Fasting blood samples will be collected in the morning of the testing day. In order to maximize the compliance and avoid the occurrence of any accident the intervention will be closely supervised by a physician, a dietitian, and an exercise physiologist.

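### The RM ANOVA main effect of treatment is not the contrast the trial was sized on and, with baseline as a level, is diluted; the interaction alone does not separate lasting benefit from rebound.

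*Protocol article*

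**What the plan says.** Under Data management and statistical analysis, the protocol article names the treatment tests in one sentence: "Repeated measures analysis of variance (RM ANOVA) will be used to analyze the main effect of treatment and potential time-by-treatment interactions". It adds that "a significance level of 0.05 will be used". It does not say which visits enter the model or which of the two tests decides, and it names no baseline covariate. The regressions in the same section relate changes in outcomes to one another; they do not compare the groups.

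On timing, the Intervention section says: "All the measurements will be conducted two days prior to, and post-intervention, and repeated two months later after the intervention". That gives three assessments, one of them before treatment.

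Under Sample size estimation, the calculation is "based on the expected fat loss following four weeks of hypoxia exposure plus exercise and dieting". Its inputs are that "the means of fat percentage decrease in the normoxia and hypoxia groups were 3.1 and 6.0% respectively" and that "the standard deviation of the change was about 3" (in per cent). The result is that "a sample size of 17 participants per group will be required to observe a similar result with a power of 80" (per cent).

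The Design section asks about short-term loss at four weeks and long-term loss at two months. The second hypothesis in the Background is that "hypoxia use will lead to less rebound of weight loss after intervention".

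**The concern.** The trial was sized on one contrast, hypoxia minus control in four-week change, and the analysis section names two other tests.

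The first, a main effect of treatment, compares each child's average over all levels of the repeated factor. If baseline is one of those levels, the average includes a visit at which randomisation makes the expected difference zero. The effect is diluted. It is also judged against the spread of fat percentage between children, which the use of change scores was meant to remove.

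The second, the time-by-treatment interaction, asks whether the two group profiles differ in shape. A benefit that lasts and a benefit that vanishes by two months both produce such a difference. That distinction is what the trial sets out to study.

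If the main effect were read as the treatment result, a real benefit of the size planned for could well be reported as not significant, with an estimate about two-thirds of the true difference or less. If the interaction p-value were read alone, it would not show whether the benefit was sustained.

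**Working it through.** **Inputs from the article.** Difference 6.0 − 3.1 = 2.9; SD of four-week change 3; 17 per group; 15% dropout; significance level 0.05 (two-sided assumed); three visits.

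**Assumptions, not in the article.** Equal variance σ² at each visit and equal correlation ρ between any two visits (compound symmetry), ρ from 0.5 to 0.9; SD of change 3 for every pair of visits; share r of the four-week effect retained at two months between 0 and 1; 17 completers per arm.

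**1. The stated sample size reproduces.** n = 2 × 3² × (1.960 + 0.842)² / 2.9² = 16.8, so 17 per group, and 17/0.85 = 20. Power at 17 is 80.5% by the normal approximation and 78.0% by the exact t-test. The 80% therefore belongs to the four-week change contrast.

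**2. Main effect with three levels.** The group differences at the three visits are 0, 2.9 and 2.9r, so the contrast is 2.9(1 + r)/3. This is 1.93 for r = 1, 1.45 for r = 0.5 and 0.97 for r = 0. From the SD of change, σ = 3/√(2(1 − ρ)). The SD of a child's three-visit mean is σ√((1 + 2ρ)/3). Two-sided noncentral-t power with 32 df:

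| ρ | σ | SD of mean | r = 1 | r = 0.5 | r = 0 |
|---|---|---|---|---|---|
| 0.5 | 3.00 | 2.45 | 61% | 39% | 20% |
| 0.7 | 3.87 | 3.46 | 35% | 22% | 12% |
| 0.8 | 4.74 | 4.42 | 24% | 15% | 9–10% |
| 0.9 | 6.71 | 6.48 | 13% | 10% | 7% |

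No cell reaches 80%.

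**3. Interaction.** This is an F test with 2 and 64 df and noncentrality λ = (n/2) × Σ(dⱼ − d̄)² / 4.5, where dⱼ is the group difference at visit j, d̄ is the mean of the three, and 4.5 = σ²(1 − ρ) = 3²/2. For r = 1 the differences are (0, 2.9, 2.9) and the sum of squares is 5.607. For r = 0 they are (0, 2.9, 0) and the sum is again 5.607. In both cases λ = 8.5 × 5.607/4.5 = 10.59 and power is 82%. For r = 0.5 the sum is 4.205, λ = 7.94 and power is 69%. With all 20 per arm retained the figures are 88%, 88% and 77%. The equality at r = 1 and r = 0 shows that the test responds alike to full persistence and to complete loss.

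**4. Baseline-adjusted four-week difference.** The residual SD is σ√(1 − ρ²): 2.60 at ρ = 0.5 and 2.92 at ρ = 0.9. Power at 17 per arm is 88% and 80% respectively, against 78% for the change-score t-test.

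**5. If baseline is not a level.** A main effect over the two post-treatment visits, unadjusted for baseline, has SD σ√((1 + ρ)/2). With r = 1 its power is 88%, 63%, 45% and 24% at ρ = 0.5, 0.7, 0.8 and 0.9. If instead the two change scores are analysed, their covariance is 4.5, so the SD of their mean is √((9 + 9 + 2 × 4.5)/4) = 2.60. The contrast is 2.9(1 + r)/2, and power is 88%, 66% and 35% for r = 1, 0.5 and 0. The change-score form avoids the dilution by baseline, but both forms still merge the two time points.

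**The case against.** A reader might infer that the planned analysis as a whole misses 80% power. The documents do not support that. The interaction is planned in the same sentence as the main effect, and it is a legitimate test of whether change differs between arms. At 17 per arm it has about 82% power with full retention or full loss. Only partial retention brings it below target (69% at one half), and the retained share is an assumption.

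A reader might also infer that the plan cannot answer its hypotheses. That is not shown either. This is a condensed article, and visit-specific contrasts after an RM ANOVA are commonly left to an analysis plan that is not at hand. No omnibus test describes the shape of an effect, and the planned means and SDs would be read beside it.

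It is fair, too, that the article does not say baseline is a level. An RM ANOVA on change scores is compatible with the text and would not average in a zero-difference visit. The main-effect powers also rest on an assumed correlation and on compound symmetry, and they range widely.

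These points narrow the finding but do not remove it. The article affirmatively names a main effect of treatment as a treatment test, and under no reading considered here is that the contrast that was sized. On the natural reading it falls short of 80% throughout the assumed range.

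**Conclusion.** The point holds in limited form. The sample size calculation is sound for the four-week change contrast, but the analysis section does not name that contrast.

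With the three stated visits as levels, the main effect of treatment reduces 2.9 by at least a third, provided the two-month effect does not exceed the four-week one. Its power at 17 per arm is then about 61% to 13% with full retention and 20% to 7% with none. These figures assume correlation 0.5 to 0.9, compound symmetry and an SD of change of 3 for every pair of visits; that baseline is a level is an inference.

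For the interaction the weakness is mainly one of interpretation: its result alone does not tell a sustained benefit from complete rebound. Whether follow-up contrasts are specified elsewhere cannot be judged from the article. The change is still worth making, because a reader who followed the main effect as written would obtain a diluted result from data that support a better-matched test.

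**What to change.** Remove the main effect of treatment as a treatment test. Fit ANCOVA at four weeks with baseline as covariate, or a mixed model on the two post-baseline visits with baseline as covariate, and name three contrasts:

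1. Hypoxia minus control at four weeks, baseline-adjusted. This is the primary contrast and corresponds to the one that was sized.
2. Hypoxia minus control at two months.
3. The difference between groups in change from four weeks to two months, for the rebound hypothesis.

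Report each with a 95% confidence interval. If an unpublished analysis plan already holds such contrasts, align the protocol wording with it and state which one is primary.

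The cost is analysis wording and SPSS syntax. It needs no new measurements and no further participants.
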